## Measurements

### Child functioning

#### Child behavior checklist (CBCL)

The CBCL is used to assess behavioral problems in children by parent’s ratings [39]. It includes 67 items in seven subscales (emotionally reactive, anxious/depressed, somatic complaints, withdrawn, aggressive behavior, attention problems, sleep problems). The first four subscales are classified as internalizing problems, and the following two are classified as externalizing problems, and this factor structure was confirmed in a Mainland China’s study, which reported correlations from 0.38 to 0.71 among the seven subscales and a correlation of 0.75 between internalizing and externalizing problems [40].

#### Strengths and weaknesses of ADHD symptoms and normal behavior rating scales (SWAN)

The scale was originally developed according to the DSM-5 diagnostic criteria for ADHD, and is completed by parents to assess their child’s attention and hyperactivity symptoms [41]. The borderline and cutoff scores were proposed in a local study [38].

#### Child attention network test (ANT)

The test is administered by a research team member and in a computer program [42]. Five fishes are presented in a horizontal row above or below the fixation point. The children are instructed to press a key to indicate in which direction the central fish is pointing and to ignore the flanking fishes. Completion of the task allows the calculation of three scores related to the efficiency of attention networks. Alerting is measured by the additional time required to respond with no cue, compared to the response time to a cue that informs the child that a target will occur shortly. Orienting is measured by the time taken to respond to a cue at the target location minus the reaction time to a central cue. Executive attention is measured as the interference effect of the flanking fish on the child’s score.

### Parent functioning

#### Parenting stress index short form (PSI-SF)

The PSI includes 36 items and was developed to reveal the sources of difficulties and the level of parenting stress [43]. The scale is divided into three subscales: parental distress, parental-child dysfunctional interaction, and difficult child. The Chinese version has been validated [44]. The reliability estimates for the total score and the three subscales were 0.92, 0.86, 0.82, and 0.86, respectively.

#### Parent heart rate variability (HRV)

The HRV is adopted to understand how psychological stress can lead to poor health status, biological data will be used together with psychological measures to evaluate the outcome of the program. Consistent research findings show that psychological distress and negative emotions affect the autonomous nervous system by inhibiting the cardiac parasympathetic system and decreasing HRV [45, 46]. HRV is a measure of cardiac autonomic function in which the cyclic variations in the RR intervals on an electrocardiogram are counted. It is also an early marker of cardiovascular risk [47]. HRV is measured by using ambulatory electrocardiogram to reflect on mother’s autonomous nervous system functioning for three minutes, using Polar heart-rate monitors (Polar Vantage NV, Polar Electro Oy, Finland). HRV is interpreted with the frequency-domain method according to the guidelines for the standard measurement and interpretation of HRV developed by a task force of the European Society of Cardiology and the North American Society of Pacing and Electrophysiology [48]. The indices of frequency-domain analysis include very-low-frequency (VLF), low-frequency (LF), and high-frequency (HF) in absolute values of power (ms2) and normalized units by using Kubios HRV (version 2.2) software.

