**Methods/design:**

A multicenter, 8-week, waitlist, randomized controlled trial of FBMI is currently being conducted in Hong Kong (from mid-2015 to mid-2016). Its effectiveness will be examined by comparing the participants who receive treatment to those in a waitlist control group. The study population consists of one hundred twenty children with ADHD, or with symptoms of inattention and hyperactivity, between 5 and 7 years of age and their parents. To be included in the study, the children are required to meet or exceed the borderline cutoff score of the Chinese version of the Strengths and Weaknesses of ADHD Symptoms and Normal Behaviors Rating Scale (SWAN-C). The primary outcome measures are the children’s ADHD symptoms and behavior and the parents’ stress. The secondary outcome measures include the children’s overall behavioral problems and performance on the Attention Network Test, the parents’ ADHD symptoms, the parents’ mindful parenting scores, and heart rate variability of parents.

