### Study objectives

The objectives of the project are (1) to reduce the symptoms of inattention and hyperactivity of children with ADHD; (2) to reduce the stress of parents; and (3) to examine the effectiveness of family-based mindfulness intervention (FBMI) in Chinese families of children with ADHD or with symptoms of inattention and hyperactivity. The following hypotheses are proposed.We expect FBMI to reduce the symptoms of inattention and hyperactivity of children relative to those in a wait-list control group.We expect FBMI to reduce the internalizing and externalizing symptoms of children relative to those in a wait-list control group.We expect FBMI to reduce parental stress, achieve better well-being, as reflected in heart rate variability (HRV) parameters, and improve parent mindfulness relative to those in a wait-list control group.

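### The HRV section records the mother, while the outcome, hypothesis and eligibility concern parents; a lesser, conditional point is VLF power from a three-minute recording

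*Protocol article*

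**What the plan says.** The section Parent heart rate variability (HRV) states that the ambulatory recording is made "to reflect on mother’s autonomous nervous system functioning". Everything else in the article refers to parents: the section's own heading, the Abstract's list of secondary outcomes ("the parents’ mindful parenting scores, and heart rate variability of parents"), and hypothesis 3 under Study objectives, which expects better parental well-being "as reflected in heart rate variability (HRV) parameters". Statistical analysis lists the sex of the parents among the baseline factors. Study sample gives inclusion and exclusion criteria for the child and an attendance requirement for parent and child, with no mother-only rule. Statistical analysis also applies intention-to-treat to every analysis and fills missing values by last-observation-carried-forward.

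On the recording itself, the HRV section covers "autonomous nervous system functioning for three minutes, using Polar heart-rate monitors" and then lists the outputs: "The indices of frequency-domain analysis include very-low-frequency (VLF), low-frequency (LF), and high-frequency (HF) in absolute values of power" and in normalized units. It gives no band limits and no minimum recording length, and defers to a cited guideline.

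**The concern.** The first problem is who is recorded. If staff follow the HRV section literally, a family whose participating parent is the father can go one of two ways. Either no HRV is taken, or the mother is recorded although she did not attend the program. In the first case the family drops out of the HRV analysis. In the second, the treatment comparison includes people who were not treated. An analysis plan cannot repair either afterwards, because the fault lies in data collection.

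The second problem is smaller. VLF oscillations are slow and the recording is short. If the slowest of them last longer than the recording, their power is not properly observed, and one of the listed indices would be hard to interpret.

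**Working it through.** **Who is recorded.** No figure in the article applies here, so the statements are set side by side.

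| Place in the protocol article | Person |
|---|---|
| HRV section, heading | parent |
| HRV section, method text | mother |
| Abstract, secondary outcomes | parents |
| Study objectives, hypothesis 3 | parents |
| Statistical analysis, baseline factors | parents, sex to be compared |
| Study sample, eligibility | parent, no restriction by sex |

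Comparing the arms on parent sex makes sense only if fathers can take part. The method text therefore conflicts with the rest whenever a father is the participating parent.

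Consequences of the literal reading:

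1. No recording for father-attended families. Carrying an observation forward needs an earlier observation, and these families would have none, at baseline or at posttest. They could not enter the HRV analysis, contrary to the commitment that all analyses follow intention-to-treat.
2. The mother recorded instead. The value exists but belongs to someone who did not receive the parent program.

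Size: the article does not say how many fathers attend. With 120 families planned, each father-attended family is 1/120 = 0.83% of the HRV sample.

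If the participating parent is fixed before randomization, a mothers-only comparison is still a comparison of randomized groups. The loss is then in numbers and in the population described, and it is not a bias in itself.

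**Three minutes and VLF.** Input from the article: 3 min = 180 s. Assumed, because the article gives no limits: a VLF band starting at 0.003 to 0.004 Hz and ending at 0.04 Hz.

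Frequency resolution = 1/T = 1/180 = 0.0056 Hz.

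Cycles in the recording = T × f:

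| f (Hz, assumed) | 180 × f |
|---|---|
| 0.003 | 0.54 |
| 0.004 | 0.72 |
| 0.01 | 1.8 |
| 0.02 | 3.6 |
| 0.04 | 7.2 |

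One full cycle fits only at or above 0.0056 Hz. Under the assumption, the part of the band below that cannot be resolved, while the upper part completes several cycles.

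Would a longer recording help? At 5 minutes, 300 × 0.003 = 0.9 cycle, still short of one cycle at the lowest assumed frequency.

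**The case against.** The strongest reply on the first point is that one stray word stands against a heading, an outcome list and a hypothesis, and reads more naturally as a slip than as a rule. That is probably right about intent. A reader might infer that a mother-only measurement is planned, and the article does not show that. The sentence is nevertheless the one that describes how the recording is made, so it should not contradict the outcome it serves.

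On VLF, the reply is that the article gives neither band limits nor a minimum length, so inadequacy cannot be shown from it. This stands, and the point is therefore conditional. A reader might go further and call VLF power from this recording mostly noise. The table does not support that: at 0.01 to 0.04 Hz the recording holds 1.8 to 7.2 cycles.

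A reader might also see a multiplicity defect. Three bands on two scales make six indices on a literal count, and six independent tests at 0.05 give 1 − 0.95^6 = 26.5% for at least one false positive. The documents do not carry that charge. HRV is a secondary outcome, and a lead index and any adjustment are commonly left to an analysis plan that is not shown here. The article does not state six, and its wording allows fewer. Nowhere does it say that one significant index confirms hypothesis 3, which also covers parental stress and mindfulness. The indices are also unlikely to be independent: with a pairwise correlation of 0.5 the figure is 20.7%, and with 0.9 it is 10.8%. Which index should lead is a matter of preference.

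**Conclusion.** The contradiction over who is recorded is real and is shown by the article alone. It is minor: it touches one secondary outcome and no primary outcome, sample size or main comparison. Its effect depends on the number of father-attended families, which is unknown; if there are none, it is only a wording error.

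The VLF point holds conditionally. If the band starts at 0.003 to 0.004 Hz, 180 s covers 0.54 to 0.72 of a cycle at the lower edge, and the slowest part of the band is out of reach. That supports caution about one index. It does not support dismissing the HRV measurement: on the same assumption, LF begins where 180 s already holds 7.2 cycles, and HF lies at higher frequencies still.

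**What to change.** 1. Reconcile the HRV section with the Abstract, Study objectives and Statistical analysis. Either state that HRV is recorded in the participating parent, the same person at every assessment, or state a mother-only restriction and carry it through the outcome definition and the HRV analysis set. The first option keeps all randomized families. The second gives up father-attended families and needs an explicit exception to the intention-to-treat statement.
2. Because the trial is already running, note for each family assessed so far which parent was recorded and which parent attended, so that any mismatch can be reported.
3. Drop VLF from the HRV outcome indices or label it exploratory, and keep LF and HF. Extending the recording by two minutes would not reach one full cycle at 0.003 Hz, so it is not a substitute.

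The cost is a wording change and a short check of existing records, with no extra participants or visits. The one loss is a secondary index if VLF is dropped.

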#### Adult ADHD self-report scale (ASRS)

The ASRS is used to assess parent inattention and hyperactivity symptoms. It includes 18 items, 9 for inattention and 9 for hyperactivity and impulsivity [49]. The Chinese version of this scale has been validated in a sample from Taiwan which showed high intraclass correlations between 0.80 and 0.85, and internal consistency with Cronbach’s alpha of 0.83 to 0.91 [50].

### Statistical analysis

The baseline characteristics of the intervention group and the waitlist control group will be compared by analysis of covariance for continuous variables and chi-square tests for categorical variables. The baseline factors include the age of the children and the parents, the sex of the children and the parents, the children’s medication status, and the SWAN scores. The effects of FBMI will be tested by analysis of covariance, comparing the FBMI group (arm 1) to the wait-list control group (arm 2). All analyses will be carried out according to the intention-to-treat approach. The participants’ missing values will be imputed using the last-observation-carried-forward method. A two-sided *P* value of 0.05 or less will be considered be statistically significant.

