## Methods/design

### Study design overview

The families of children with diagnoses of ADHD or with symptoms of inattention and hyperactivity are being recruited to participate in this study. The rationale for not restricting the study to children with formal diagnoses was that many children are first assessed by professionals after 6 in Hong Kong, and therefore many children with severe inattention and hyperactivity symptoms have not yet received a diagnosis.

A flowchart of the recruitment and implementation of this waitlist randomized controlled trial is illustrated in Fig. 1. All eligible families are randomized into a treatment group or a wait-list control group. The FBMI is delivered in a group format. All families in the waitlist control groups will undergo the same program after the posttest of the treatment groups. Three local non-government organizations in Hong Kong are participating in the study. The programs are conducted in the three collaborators’ district family service centers.

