### Study sample

One hundred twenty children between 5 and 7 years of age with ADHD or with symptoms of inattention and hyperactivity and their parents are being recruited to participate in the FBMI. During the screening interview, all outcome measures and demographic information are completed by the parents. The inclusion criteria include (1) children age between 5 and 7 years and (2) a score that meets or exceeds the borderline cutoff of the Strengths and Weaknesses of ADHD Symptoms and Normal Behaviors Rating Scale (SWAN) [38]. The exclusion criteria include (1) children with another developmental disability, such as an intellectual disability or autism spectrum disorder, and (2) the inability of either the parent or the child to attend 80 % of the program sessions.

The randomization procedure is as follows. A 10 × 10 table was created by randomly assigning digits 0 to 9. One row of the table is randomly selected, and the sequence of digits in that row is observed. A participant list is prepared, and the sequence of participants is observed. The first digit will determine the first participant’s group, and so on. Participants with an even digit are assigned to the intervention group, and those with an odd digit are assigned to the control group. After the families are assigned to groups, another research team member contacts the parents by phone, to inform the parent about the results of randomization and to confirm that both the parent and the child will participate in the study. It means that team member who interviews the families is blinded in the assignment process.

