### Estimation of sample size

Because no studies of FBMI have been performed in the families of young children with ADHD, and because the effect sizes of studies of psychosocial treatments vary, the research team adopted an estimated effect size of 0.6 for changes in child attention and behavior. Based on a one-sided type I error of 5 % and 80 % power to detect statistically significant differences between the FBMI and wait-list control groups, the required sample size per arm is 45. Considering an attrition rate of 15 %, more than one hundred six families should be recruited for the study.

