## Discussion

Although ADHD is one of the most common mental disorders in early childhood, existing treatments have limitations, and the families of children with ADHD experience high levels of stress that create a great burden to school systems and the community [52, 53]. Poor management of child behavior and family relationships further increase the risks of other comorbid psychopathologic conditions, such as oppositional defiant disorders and conduct disorders in children and major depressive disorders in caregivers [54, 55]. The search for effective treatments to improve the functioning and quality of life of families of children with ADHD should be a priority in the mental health care and education sectors.

We are conducting the first randomized controlled trial of FBMI in Chinese families that contains multiple outcome measures with biomarkers and child attention test. The study includes multiple sites and recruits one hundred twenty families, based on an estimation of the expected effect size. Successful completion of this study and confirmation of the hypotheses will contribute to the evidence base regarding FBMI and treatment options to ADHD. The application of FBMI may also be considered for children with other clinical problems, such as autism spectrum disorder, severe behavioral problems, conduct disorders, depression, and anxiety. Further studies should also consider a 6-month or 1-year follow-up period to verify the sustainability of the treatment effects. Treatment designs that can compare the effects and costs of medication, behavior training, and other methods will be the next step in investigating the efficacy of FBMI.

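### Last observation carried forward replaces a missing posttest with the screening score, which shrinks the estimated effect and can bias it in either direction when dropout differs by arm

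*Protocol article*

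**What the plan says.** The Statistical analysis section gives one rule for missing data: "missing values will be imputed using the last-observation-carried-forward method". It applies within an intention-to-treat analysis ("All analyses will be carried out according to the intention-to-treat approach"), and the treatment effect is tested by analysis of covariance of FBMI against wait-list. The covariates are not named.

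Three places show which observation would be carried forward:
- Study sample: "During the screening interview, all outcome measures and demographic information are completed by the parents". This is the assessment before randomization.
- Study design overview: "All families in the waitlist control groups will undergo the same program after the posttest of the treatment groups". The randomized comparison therefore ends at the posttest.
- Discussion: "Further studies should also consider a 6-month or 1-year follow-up period to verify the sustainability of the treatment effects". Longer follow-up is left to later trials.

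The text describes no assessment between screening and posttest.

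Estimation of sample size uses an effect of 0.6, finds 45 per arm, allows for 15% attrition without splitting it by arm, and concludes that "more than one hundred six families should be recruited for the study". Planned recruitment elsewhere in the article is 120 families, in five cycles of 24.

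**The concern.** With one measurement before and one after, carrying the last observation forward means carrying the baseline forward. Every family that leaves is recorded as unchanged, whichever arm it was in and whatever happened to the child afterwards. The article gives no reason to expect that.

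For SWAN the assumption is especially doubtful. Children enter by reaching a cutoff on that scale, and scores selected for being extreme tend to drift back in both arms. Carry-forward removes the drift for dropouts only.

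Two consequences follow. The treatment effect is diluted by the dropout fraction. If the dropout fraction differs between arms, any change common to both arms is also turned into a difference between them. Unequal dropout is possible here: families are told their arm by phone before they confirm participation, and one arm attends weekly sessions while the other waits. The rule applies to every primary outcome.

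**Working it through.** **Inputs from the article.** Effect 0.6 (standardized, so SD = 1), 80% power, 45 per arm, 15% attrition, more than 106 families as a minimum, 120 planned, two-sided 0.05 in the analysis.

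**Assumptions.** 60 per arm (1:1 split of 120), analysis of covariance on the baseline score, pre-post correlation r, equal SD at both times, dropout at random, and the arm-specific dropout rates and common time trends shown below.

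**1. The plan's own figures.** A two-sided 5% t-test at 80% power needs 44.6, so 45 per arm, which reproduces the plan. The article labels the error one-sided, which would give about 36. That is a separate point and does not affect this one. Attrition: 45 / 0.85 = 52.9, so 53 per arm and 106 in total. This step treats dropouts as lost and keeps the effect at 0.6. Carry-forward does the reverse: it keeps dropouts in the analysis and gives them no change.

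**2. Expected estimate under carry-forward.** Let d be the true effect, m the improvement common to both arms, and pT and pC the dropout in FBMI and wait-list. Then

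estimate = (1 − pT)(d + m) − (1 − pC)m.

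| pT / pC | d | m | Calculation | Estimate |
|---|---|---|---|---|
| 15% / 15% | 0.60 | any | 0.85 × 0.60 | 0.51 |
| 10% / 20% | 0 | 0.3; 0.5 | (0.90 − 0.80)m | 0.03; 0.05 |
| 5% / 25% | 0 | 0.3; 0.5 | (0.95 − 0.75)m | 0.06; 0.10 |
| 25% / 5% | 0.60 | 0.3 | 0.75 × 0.90 − 0.95 × 0.30 | 0.39 |
| 5% / 25% | 0.60 | 0.3 | 0.95 × 0.90 − 0.75 × 0.30 | 0.63 |
| 25% / 5% | 0.60 | 0 | 0.75 × 0.60 | 0.45 |
| 5% / 25% | 0 | 0 | 0 | 0 |

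Simulation at 60 per arm reproduces these values. Analysis of covariance on the observed posttests stays at about 0.60, or about 0 when there is no effect.

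**3. Type I error (60 per arm, r = 0.6, two-sided 5%).**
- 10%/20% dropout, m = 0.3 to 0.5: about 5.5% to 6.5%.
- 5%/25% dropout, m = 0.3 to 0.5: about 7% to 11%.
- Equal dropout, or no time trend: about 5%.
- Observed-data analysis of covariance in the same settings: about 5%.

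**4. Power with 15% dropout in each arm.** For an unadjusted t-test at 0.51 SD, power is 74% with 53 per arm and 79% with 60. The plan specifies analysis of covariance, and with baseline as covariate and m = 0.3 the picture changes:

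| r | Per arm | Carry-forward | Observed data |
|---|---|---|---|
| 0.6 | 60 | 94% | 96% |
| 0.6 | 53 | 91% | 94% |
| 0.3 | 60 | 83% | 88% |
| 0.3 | 53 | 79% | 84% |

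The loss is about 2 to 5 points.

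**The case against.** Several points on the other side are sound.

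**Power.** A reader might infer from the diluted 0.51 SD that the trial is underpowered, at 74% or 79%. The article does not support that. Those figures belong to an unadjusted test, while the plan specifies analysis of covariance. The 74% also takes the minimum of 106 as the trial size, although 120 families are planned. Baseline adjustment is itself inferred, because the covariates are not named, but it is the usual meaning of the method in a pre-post design.

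**False positives.** A reader might also infer that the rule will produce a false benefit. That needs more dropout in the wait-list arm together with improvement in both arms, and the article states neither. The 5%/25% split is an extreme assumption, and at 10%/20% the inflation is small. Wait-list families have the program still to come, which is a reason to stay, so higher dropout under FBMI is at least as plausible. In that case the benefit is understated.

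**Conservatism.** Carry-forward is sometimes defended as conservative. The 0.63 in the table shows that it need not be.

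**Scope.** Selection on a high score applies directly only to SWAN. For parenting stress and the other outcomes a common time trend is possible, but it does not follow from the entry criterion.

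**Schedule.** The schedule figure is not shown, so an intermediate assessment cannot be ruled out. All the relevant text points to a single posttest.

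None of this defends the rule itself. It is fixed in the article, no argument is given that dropouts stay at baseline, and the dilution to 0.51 needs only the plan's own attrition rate, with dropout unrelated to outcome.

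**Conclusion.** The point holds as a fault in the stated missing-data method, and its main harm is a biased estimate. With 15% dropout in both arms, a true 0.60 SD is reported as about 0.51 SD whatever the common time trend, and the sample size section does not allow for this.

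With unequal dropout and a shift in both arms, the bias goes in either direction. Its size rests on assumptions that the article does not supply: a false difference of 0.03 to 0.05 SD at 10%/20%, 0.06 to 0.10 SD at the extreme 5%/25%, and an estimate of 0.39 SD instead of 0.60 at 25%/5% with a 0.3 SD common improvement. With no true effect and either equal dropout or no time trend, there is no bias.

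The documents do not support a stronger claim that the trial lacks power or that its type I error is badly inflated. The conclusion assumes that there is no assessment between screening and posttest.

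**What to change.** Replace carry-forward as the primary method with an analysis of all randomized families that is valid under missing at random. Either of these would do:
- a likelihood-based model of the screening and posttest scores together; or
- multiple imputation by arm, using the baseline scores and the baseline factors the article already lists (ages and sexes of children and parents, the child's medication status, SWAN).

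With one score before and one after, analysis of covariance on the observed posttests gave nearly unbiased results in the check above, so the choice between these methods matters less than dropping carry-forward. Keep carry-forward, if at all, as a labelled sensitivity analysis. The attrition step in the sample size section then matches the analysis, since dropouts are no longer counted as having no change.

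The cost is a change of analysis wording and slightly larger standard errors. No extra families, visits or data are needed. Missing at random is itself an assumption and should be stated as one.
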